### Sample size calculation

The primary outcome is the time to recover following surgery. A difference of 7 days was considered a clinically significant difference based on time to recover following TAH (28.1 days, SD 9.5), VH (21.3 days, SD 8.5) and LAVH (19.7 days, SD 7.5 days) in a study published in the *BJOG* by Ottosen et al. [7]. Using the mean and SD of the above data, a type 1 error of 0.01 and a power of 80% with a loss to follow-up of 20% produces a sample size of 49 patients per arm (total of 147). The reason for a type 1 error of 0.01 (two-sided) was for a Bonferroni adjustment for multiplicity to keep the overall *p* value to less than 0.05 after pairwise comparisons.

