**Methods:**

A multicentre three-armed randomized control trial is being conducted at the professorial gynaecology unit of the North Colombo Teaching Hospital, Ragama, Sri Lanka and gynaecology unit of the District General Hospital, Mannar, Sri Lanka. The study population is women needing hysterectomy for non-malignant uterine causes. Patients with a uterus > 14 weeks, previous pelvic surgery, those requiring incontinence surgery or pelvic floor surgery, any medical illness which caution/contraindicate laparoscopic surgery and who cannot read and write will be excluded. The main exposure variable is non-descent vaginal hysterectomy and total laparoscopic hysterectomy. The control group will be patients undergoing total abdominal hysterectomy. The primary outcome is time to recover following surgery, which is the earliest time to resume all of the usual activities done prior to surgery. In total, 147 patients (49 per arm) are needed to have 80% power at α-0.01 considering a loss to follow-up of 20% to detect a 7-day difference between the three routes; TLH versus TAH versus NDVH. The economic evaluation will take a societal perspective and will include direct costs in relation to allocation of healthcare resources and indirect costs which are borne by the patient. A micro-costing approach will be adopted to calculate direct costs from the time of presentation to the gynaecology clinic up to 6 months after surgery. Incremental cost-effectiveness ratios (ICER) will be obtained by calculating the incremental costs divided by the incremental effects (time to recover and QALYs gained) for the intervention groups (NDVH and TLH) over the standard care (TAH) group.

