### Data analysis

All randomized patients will be included in the analyses. A single principal analysis will be done comparing the three arms (TAH, NDVH and TLH) 12 months after the last woman has had her operation. The fact that the trial will be conducted at two centres will be taken into account during data analysis.

A Kaplan–Meier survival analysis will be done for the primary outcome which is time to recover following hysterectomy. The end-point is the actual time to recover. It will be assessed and documented at the 6-week clinic visit. Patients who have not recovered by 6-weeks will be followed-up beyond 6-weeks to detect complications and the actual time to recover. Post hoc pairwise analysis between TAH, NDVH and TLH will be done using COX regression.

Other outcomes that need follow-up; QALYs, urinary, vaginal and bowel functions will also be analysed using Kaplan Meier survival analyses. The end point for QALYs is 6-months while for urinary, vaginal and sexual function it is 1-year. Patients who do not complete follow-up in these secondary outcomes will be right censored up to their respective end-points. Post hoc pairwise analysis between TAH, NDVH and TLH will be done using COX regression. The other outcomes; operative time, anaesthesia time, postoperative hospital stay, cost, pain scores and blood loss will be analysed using Kruskal-Wallis test with post hoc comparisons. The complications will be described for each category. A fully specified Statistical Analysis Plan will be provided before opening the database.

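### The stated 80% power belongs to a comparison of mean days; it is not established for the planned Cox comparisons, which also give no difference in days

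*Protocol article*

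**What the plan says.** **Protocol article, Sample size calculation.** The threshold is in days: "A difference of 7 days was considered a clinically significant difference based on time to recover". The inputs are means and standard deviations from one cited study: "TAH (28.1 days, SD 9.5), VH (21.3 days, SD 8.5) and LAVH (19.7 days, SD 7.5 days". The calculation is described as "Using the mean and SD of the above data, a type 1 error of 0.01 and a power of 80" per cent, and "with a loss to follow-up of 20% produces a sample size of 49 patients per arm (total of 147"). The level is explained thus: "The reason for a type 1 error of 0.01 (two-sided) was for a Bonferroni adjustment for multiplicity".

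**Protocol article, Abstract (Methods).** The power is said to be "to detect a 7-day difference between the three routes; TLH versus TAH versus NDVH".

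**Protocol article, Data analysis.** Time to recover is analysed by Kaplan–Meier, and then "Post hoc pairwise analysis between TAH, NDVH and TLH will be done using COX regression". Follow-up does not stop at the clinic visit: "Patients who have not recovered by 6-weeks will be followed-up beyond 6-weeks to detect complications and the actual time to recover".

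**Protocol article, Economic evaluation.** Incremental cost-effectiveness ratios of each intervention against TAH use time to recover, as well as QALYs, as the effect.

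**The concern.** The article fixes both the basis of the power and the pairwise test for the same primary outcome, and the two do not match. The first is a difference in mean days. The second is a hazard ratio. Nothing converts one to the other: there is no target hazard ratio, event count or assumed distribution of recovery times.

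Two things are at stake. First, a reader takes the 80% to describe the planned test, and it may not. Second, the clinical threshold is 7 days and one cost-effectiveness ratio needs incremental days, yet the only pairwise method named yields neither a difference in days nor its interval. Heavy censoring does not force this choice, because women who have not recovered at 6 weeks are followed until they do.

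A smaller matter is the abstract's wording, which lets the power statement be read as expecting a 7-day gap for every pair. The cited figures show a gap of about that size only against TAH.

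**Working it through.** **1. Reproduce the plan's figure.** Inputs from Sample size calculation: difference 7 days, SDs 9.5 (TAH) and 8.5 (VH), two-sided 0.01, power 80%, loss 20%.

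- Common SD = √[(9.5² + 8.5²)/2] = √81.25 = 9.01.
- n per arm = 2(z₀.₉₉₅ + z₀.₈₀)² × SD²/δ² = 2(2.576 + 0.842)² × 81.25/49 = 38.7, so 39.
- 39/0.8 = 48.75, so 49 per arm and 147 in all.

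The stated size is a comparison-of-means size. At the cited TAH–VH difference, 28.1 − 21.3 = 6.8 days, the same 39 per arm gives Φ[6.8/(9.01√(2/39)) − 2.576] = Φ(0.755) = 77.5%.

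**2. What Cox regression would need.** If all 39 evaluable women per arm have an observed recovery, each pair has 78 events. By Schoenfeld's formula, 80% power at two-sided 0.01 needs HR = exp[2(2.576 + 0.842)/√78] = exp(0.774) = 2.17. A hazard ratio of 2.0 would need 98 events and has 69% power at 78. A ratio of 1.75 has 46%.

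**3. Power of the planned test at the cited figures.** The article gives no distribution, so several were simulated: 39 per arm, all recoveries observed, two-sided 0.01, 3,000 to 5,000 trials per setting. The log-rank test is the score test of a Cox model with treatment alone.

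| Shape assumed, TAH vs VH | Cox / log-rank | t-test |
|---|---|---|
| Normal | 75–78% | 76% |
| Weibull, shape fitted to each arm | 71–73% | 75–76% |
| Gamma | 64–67% | 75% |
| Lognormal | 63–67% | 75–77% |
| Weibull, common shape (proportional hazards), 6.8 days | 82–84% | 74–75% |
| Same, 7 days | 85% | 78% |
| Gompertz, constant HR 2.44 (proportional hazards) | 88% | 74% |

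The first four rows match the cited means and SDs in both arms. The common-shape Weibull keeps only the average variance, with SDs of about 10.2 and 7.7. The Gompertz is fitted to TAH (28.1, SD 9.5), and its other arm comes out at 21.3 days, SD 8.6, against the cited 21.3 and 8.5.

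Sensitivity:

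- Seven days with SD 9.01 in both arms, first four shapes: Cox 59–70%.
- Recording whole days lowered the Cox Wald figures for the first four shapes by 2 to 4 points in one set of runs, to 60–72%.
- Censoring at day 42 changed Cox power by under 2 points.
- No loss at all (49 per arm), first four shapes: Cox 75–86%.

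**4. The other pairs.**

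- TAH vs LAVH: 28.1 − 19.7 = 8.4 days. Cox or log-rank power is about 90–98% over the first four shapes.
- VH vs LAVH: 21.3 − 19.7 = 1.6 days, SD √[(8.5² + 7.5²)/2] = 8.02. Means-based power is about Φ[1.6/(8.02√(2/39)) − 2.576] = Φ(−1.69), or roughly 5%.

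**5. How much censoring to expect.** If times were normal, P(T > 42 days) is 7% for TAH and under 1% for VH, and those women are followed further.

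**The case against.** The strongest reply is that the cited figures cannot settle how Cox regression performs. That stands. A reader might infer from the means and SDs that hazards are non-proportional, for instance because a normal model gives a hazard ratio that falls over time. But two moments do not fix a distribution, and the Gompertz example reproduces the cited figures almost exactly with a constant hazard ratio. Nor do the documents support saying that Cox regression fails to deliver 80%. Under proportional hazards it does better than the t-test, and against LAVH it passes 90%.

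A reader might also infer that TLH against NDVH has almost no power. The 1.6 days is LAVH against VH; no TLH figure is given, and power for a true 7-day difference applies to any pair. The stated hypothesis and the cost-effectiveness ratios are against TAH.

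It is also fair that time-to-event methods suit this outcome with 20% loss planned, that Kaplan–Meier curves show recovery in days by arm, and that the promised analysis plan may add summaries. This narrows the point but does not remove it. The article itself attaches 80% to one analysis and names another, and curves by arm are not a pre-specified pairwise difference with an interval.

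**Conclusion.** The mismatch is certain, because 49 per arm follows exactly from a means formula. Its effect on power is uncertain. For TAH against NDVH, taking the VH figures as its proxy, the planned test has roughly 63–78% power under four common shapes and 82–88% under two proportional-hazards shapes. The correct statement is that 80% is not established for the planned test, not that it is missed. The means-based comparison itself has about 74–78% at the cited 6.8 days.

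The lack of a pairwise estimate in days holds whatever the distribution, because both the threshold and one cost-effectiveness ratio are in days. The power figures assume 39 evaluable women per arm with observed recovery times, and that the cited study's figures carry over to this trial. The point deserves correction but does not threaten the design.

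**What to change.** 1. Specify the pairwise difference in mean days to recovery as the primary contrast: a difference in restricted mean survival time to a fixed horizon, adjusted for centre. A horizon of 3 or 6 months would lie beyond nearly all expected recoveries. At the least, pre-specify it as the estimate reported alongside Cox regression. Keep the Kaplan–Meier curves.
2. Use the same estimate as the effect in the time-to-recover cost-effectiveness ratio.
3. Restate the power. Either say that it is that of the means-based comparison (80% at 7 days, about 74–78% at the cited 6.8 days) or, if Cox regression stays primary, give and justify the hazard ratio it needs, about 2.17 with 78 events per pair.
4. State that the cited data support a difference of about 7 days only against TAH. Report TLH against NDVH as an estimate with its interval, and draw no conclusion of equivalence from a non-significant result.

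The cost is wording and analysis code, settled before the database is opened. Patients and data are unchanged. The drawback is a slightly less favourable power statement. The restricted-mean test was not simulated here; with nearly complete follow-up its power should be close to that of the means comparison, and this should be confirmed for the horizon chosen.

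### The 0.01 level is justified as Bonferroni for pairwise comparisons of three arms, but Bonferroni gives 0.05/3 = 0.0167; the stricter level costs about 5 points of power

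*Protocol article*

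**What the plan says.** All the inputs are in the protocol article, under Sample size calculation.

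- Target: "A difference of 7 days was considered a clinically significant difference based on time to recover following TAH" and the two other routes. The abstract repeats the target: "147 patients (49 per arm) are needed to have 80% power" and, later in the same sentence, "to detect a 7-day difference between the three routes".
- Source data: "TAH (28.1 days, SD 9.5), VH (21.3 days, SD 8.5) and LAVH (19.7 days, SD 7.5 days").
- Calculation: "Using the mean and SD of the above data, a type 1 error of 0.01 and a power of 80" per cent, with 20% loss to follow-up, "produces a sample size of 49 patients per arm (total of 147").
- Level: "The reason for a type 1 error of 0.01 (two-sided) was for a Bonferroni adjustment for multiplicity". The stated aim is an overall level under 0.05 once the pairwise comparisons are made.

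The Data analysis section names those comparisons: pairwise between TAH, NDVH and TLH, by Cox regression. It also says that a full statistical analysis plan will come before the database is opened.

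**The concern.** The article gives both the rule (Bonferroni, overall level 0.05, pairwise comparisons) and the result (0.01). Three arms have three pairs, and Bonferroni then gives 0.05/3, not 0.01. The level decides whether each primary comparison counts as significant, and it also enters the sample size. If it is stricter than its own justification requires, the trial gives up power for no stated reason, and a pairwise p-value between 0.01 and 0.0167 would be declared non-significant although the stated rule would accept it.

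A lesser point sits beside it. The calculation is attributed to the mean and SD of the cited data, yet the TAH and VH means quoted there are 6.8 days apart, not 7. The reader cannot tell from that sentence which difference the 80% belongs to.

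**Working it through.** **Inputs.** SDs 9.5 (TAH) and 8.5 (VH); target 7 days; two-sided 0.01; power 80%; loss 20%. All are from Sample size calculation. Sum of variances: 9.5² + 8.5² = 90.25 + 72.25 = 162.5.

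**Step 1: reproduce the 49.** Evaluable n per arm = (z for alpha + z for power)² × 162.5 / d².

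- d = 7: (2.576 + 0.842)² × 162.5 / 49 = 38.73, so 39. Then 39 / 0.8 = 48.75, so 49 per arm and 3 × 49 = 147. This matches exactly.

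**Step 2: the stated level against its rule.**

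- Pairs among three arms: TAH-NDVH, TAH-TLH, NDVH-TLH, so 3.
- Bonferroni: 0.05 / 3 = 0.0167.
- Number of tests for which Bonferroni gives 0.01: 0.05 / 0.01 = 5. The article counts no five comparisons.
- Counting only the two comparisons with TAH would give 0.05 / 2 = 0.025, further from 0.01.
- Upper bound on overall error with three tests at 0.01: 3 × 0.01 = 0.03.

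**Step 3: what the stricter level costs.** Evaluable per arm: 49 × 0.8 = 39.2, taken as 39. Standard error of the difference: √(162.5 / 39) = 2.041 days. Normal-approximation power is Φ(d / 2.041 − z), with z = 2.576 at 0.01 and 2.394 at 0.05/3. For example, at 7 days: Φ(3.429 − 2.576) = 80.3% and Φ(3.429 − 2.394) = 85.0%. The t column uses the noncentral t distribution.

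| Difference | Two-sided level | Power, normal | Power, t |
|---|---|---|---|
| 7 days (stated target) | 0.01 | 80.3% | 78.2% |
| 7 days | 0.05/3 | 85.0% | 83.4% |
| 6.8 days (28.1 − 21.3) | 0.01 | 77.5% | 75.3% |
| 6.8 days | 0.05/3 | 82.6% | 80.9% |

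The loss from using 0.01 is 4.7 to 5.2 points at 7 days and 5.1 to 5.6 points at 6.8 days.

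**Step 4: the 6.8-day reading.** With d = 6.8 at 0.01, n = (2.576 + 0.842)² × 162.5 / 46.24 = 41.04, so 42 evaluable, and 42 / 0.8 = 52.5, so 53 per arm. At 0.05/3 with a t-test, 6.8 days needs 39 evaluable, and 39 / 0.8 gives 49 per arm. At the level its own rule implies, the planned size is therefore enough on either reading of the difference.

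**The case against.** The strongest defence is that 0.01 does what the article says it should: it keeps the overall level below 0.05. Three tests at 0.01 bound it at 0.03. The sample size was computed at 0.01, so the cost of strictness is already paid, and the 7-day target is met at about 80%. Relaxing a published threshold in a trial that is already recruiting also needs a reason. All of this is correct. It shows that the level is safe, but not that it is the Bonferroni level it is said to be.

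Two stronger readings are tempting, and the document does not support them.

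- A reader might infer that 49 per arm is an arithmetic error, that 53 are needed, and that the real power is 75-78%. Those figures appear only when 6.8 days replaces the target. Both the abstract and the sample size section give 7 days, and 49 follows exactly from it. A target based on earlier data need not equal the observed difference to one decimal place.
- A reader might infer that the abstract's claim about the three routes fails, because the quoted VH and LAVH means differ by only 1.6 days (21.3 − 19.7), where power at 0.01 is about 4-5%. But the abstract claims power for a 7-day difference. With 39 evaluable at 0.01 (normal approximation), 7 days has about 80% power for SDs 9.5/8.5, 85% for 9.5/7.5 and 90% for 8.5/7.5, so the claim holds for all three pairs. The objectives hypothesise only that TLH and NDVH are better than TAH, and no equivalence claim is planned.

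**Conclusion.** The sample size stands. What does not stand is the stated origin of the 0.01: Bonferroni for three pairwise comparisons at an overall 0.05 is 0.0167. The discrepancy is on the conservative side. It does not inflate type 1 error, and it costs about 5 points of power in the least favourable pair (TAH against VH). The sentence attributing the calculation to the quoted means is loose wording: at 0.01 the 80% holds for 7 days under the normal approximation (78.2% by t), and for the quoted 6.8 days it is 75-78%.

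These figures assume a two-sample comparison of means, the SDs of the cited study, 39 evaluable patients per arm and three comparisons in the family. The planned analysis is Kaplan-Meier and Cox regression. Its power depends on the shape of the recovery-time distribution, which the article does not give, so no shortfall in a stated figure can be shown from that side.

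**What to change.** Before the database is opened, in the statistical analysis plan that the article promises:

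1. Test the three pairwise comparisons of time to recover at two-sided 0.05/3. Write the level as the fraction, because 3 × 0.0167 is 0.0501. Overall error remains at most 0.05.
2. Restate the power with 39 evaluable per arm: about 83-85% for a 7-day difference and 81-83% for the quoted 6.8 days (t and normal). Leave 49 per arm and 147 in total unchanged.
3. Say that the calculation used a 7-day target with the SDs of the cited study.

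The cost is wording, no patients, and a threshold less strict than the published one. The change should therefore be dated and explained as bringing the level into line with its stated rule. If 0.01 is kept, the alternative is to describe it as stricter than Bonferroni for three comparisons and to state that the 80% applies to a 7-day difference under the normal approximation.

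### The two-sided 0.01 is presented as a Bonferroni adjustment for the pairwise comparisons, but three comparisons give 0.0167; the slip is conservative and costs power only if 0.01 becomes the analysis threshold

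*Protocol article*

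**What the plan says.** The Sample size calculation section of the protocol article uses "a type 1 error of 0.01 and a power of 80% with a loss to follow-up of 20" per cent to reach 49 women per arm, 147 in total. It adds: "The reason for a type 1 error of 0.01 (two-sided) was for a Bonferroni adjustment for multiplicity", the aim being to hold the overall p "value to less than 0.05 after pairwise comparisons". The effect to be detected is 7 days: "A difference of 7 days was considered a clinically significant difference". The supporting data are "TAH (28.1 days, SD 9.5), VH (21.3 days, SD 8.5) and LAVH (19.7 days, SD 7.5 days".

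The Abstract (Methods) describes the target as "to detect a 7-day difference between the three routes; TLH versus TAH versus NDVH". The Data analysis section plans one principal three-arm comparison, with Kaplan–Meier analysis of time to recover, and then: "Post hoc pairwise analysis between TAH, NDVH and TLH will be done using COX regression". It names no significance level for these tests and does not make the three-arm comparison a condition for the pairwise ones. It defers full detail to a Statistical Analysis Plan. The Objectives section states a narrower hypothesis: that the laparoscopic and vaginal routes are each better than the abdominal one.

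**The concern.** The stated reason does not produce the stated level. Three arms form three pairs, and Bonferroni divides 0.05 by three. If the family is only the two comparisons against abdominal hysterectomy, it divides by two. A divisor of five matches nothing in the article.

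This goes beyond wording because 0.01 is the figure on which the sample size rests. It also leaves the analysis threshold unclear. An analyst who follows the number would test each pair at 0.01, and one who follows the reason would test at 0.0167. A pairwise p value between the two would count as significant under one reading and not under the other. If the stricter level is adopted, the trial uses less of its error allowance than its own rule permits and loses power on its primary outcome.

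**Working it through.** **Inputs**, all from the Sample size calculation section: two-sided level 0.01; power 80% (z = 0.8416); difference 7 days; SDs 9.5 (abdominal) and 8.5 (vaginal); loss to follow-up 20%. The number of pairs, three, comes from the Data analysis section.

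**1. The plan's own figure.** n = (z₁₋α/₂ + z₀.₈₀)² × (SD₁² + SD₂²) / d²

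- α = 0.01: (2.5758 + 0.8416)² × (90.25 + 72.25) / 49 = 38.7, so 39 completers; 39/0.80 = 48.75, so 49 per arm; 3 × 49 = 147. This matches exactly.

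**2. The level.**

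- Three pairs: 0.05/3 = 0.0167.
- Two comparisons against abdominal hysterectomy: 0.05/2 = 0.025.
- 0.01 = 0.05/5.

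**3. The error actually spent.** Three tests at 0.01 spend at most 3 × 0.01 = 0.03. Simulation under the global null (100,000 runs, 39 per arm, normal data, the cited SDs) gives an overall error of about 2.7% for pairs at 0.01, about 4.4% for pairs at 0.0167, and about 5.0% for a three-arm F test at 0.05 followed by pairs at 0.05. With equal SDs these are 2.6%, 4.3% and 4.9%. When only one pair is truly equal, the closed test rejects that pair in about 5% of runs.

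**4. Power with the same 147 women** (39 completers per arm, abdominal versus vaginal, 7 days). The standard error is √(162.5/39) = 2.041, and 7/2.041 = 3.429.

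| Rule | Normal approximation | t-test |
|---|---|---|
| Pairs at 0.01 | Φ(3.429 − 2.576) = 80.3% | 78.2% |
| Pairs at 0.0167 | Φ(3.429 − 2.394) = 85.0% | 83.4% |
| Three-arm test at 0.05, then pairs at 0.05 | – | about 88–91% (simulated) |

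The closed-test figure depends on the third arm. It is about 91% when both newer routes are 7 days faster than abdominal hysterectomy, and about 88% when the third arm lies midway between the other two. In the first of these settings, the power to show both newer routes better than abdominal hysterectomy is about 70%, 77% and 89% under the three rules.

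**5. Sample size had 0.0167 been used.** By the plan's normal approximation: (2.3940 + 0.8416)² × 162.5/49 = 34.7, so 35; 35/0.80 = 43.75, so 44 per arm; 132 in total, 15 fewer. By the t-test, 35 completers give 78.4%, and 80% needs 37; 37/0.80 = 46.25, so 47 per arm, 141 in total. The two methods should not be mixed: the t-test equivalent at 0.01 is 41 completers, so 52 per arm.

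**6. The planned type of analysis.** The figures above are for means, whereas the article plans Kaplan–Meier and Cox. A smaller log-rank simulation (6,000 runs, 39 per arm, no censoring) gave 78.5%, 83.5% and 91.8% for the same three rules at 7 days. Null error was slightly higher under every rule (3.2%, 5.1% and 5.6%), which points to the large-sample test at this size and not to the gate.

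**The case against.** The strongest reply is that nothing the article promises is broken. It promises an overall error below 0.05, and three tests at 0.01 keep that promise with room to spare. It reports 49 per arm at 0.01, and that is right. A sponsor may choose a stricter level than Bonferroni requires. The Data analysis section sets no level for the pairwise tests, and the Statistical Analysis Plan, not shown, may settle the matter. A closed test is a different design choice, not the correction of an error.

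Much of this stands, and it rules out three stronger readings. A reader might infer that type 1 error is not controlled, or that 147 is miscalculated; the arithmetic supports neither. A reader might also infer that 7-day differences would be missed in one trial in five because of this slip. That rate is simply the 80% power the plan chose. Changing the divisor moves power by about 5 points, from 80% to 85%.

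What does not stand is that the matter belongs wholly to the analysis plan. The article does not merely omit a threshold. It states one, gives a reason that yields a different one, and sizes the trial on it.

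**Conclusion.** The Bonferroni justification for 0.01 is wrong: the pairwise family in the article gives 0.0167, and the narrower family gives 0.025. The consequence is lost efficiency, not a loss of validity. If 0.01 becomes the analysis threshold, about 5 percentage points of power are given up relative to Bonferroni for three pairs, and roughly 10 to 13 points by t-test relative to a closed test (88–91% against 78%).

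This rests on 39 completers per arm, a true 7-day difference, the cited SDs, and calculations on means. The exact gain under log-rank or Cox analysis may differ somewhat. If the analysis plan already sets 0.0167 or a gated procedure, no power is lost and only the stated reason needs correcting. No choice of level helps the vaginal versus laparoscopic comparison at the cited difference of 21.3 − 19.7 = 1.6 days, where power is about 4% at 0.01 and 14% even at 0.05.

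**What to change.** Keep 147 and choose one of two routes, fixed in writing before the database is opened.

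- **Minimum correction.** State that the three pairwise comparisons are tested at two-sided 0.05/3 (Bonferroni, or Holm, which is never less powerful), and restate the power as about 83–85% for 7 days with 39 completers per arm.
- **Closed test.** State that the three-arm test of time to recover is done at 0.05 and, only if it is significant, each pair is tested at two-sided 0.05. With exactly three groups this controls the overall error: if all arms are equal the gate holds it at 0.05, and if only one pair is equal only one true null remains. It fits the order already in the Data analysis section; the gate and the levels need to be added.

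Neither route needs more women or new data. The cost is a dated, justified amendment, which matters because the trial is open-label and already recruiting. Under the closed test, simultaneous intervals at 0.0167 will not always agree with the test decisions, and the report should say so.
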